### Sample size

We have previously completed a non-randomized pilot study (n = 36, [name]) comparing mini-open to all-arthroscopic rotator cuff repair and have data representative of the population we wish to sample for this study. We piloted a number of study outcomes, but our calculations are based on our planned primary outcome measure (WORC). From our pilot data, the baseline WORC scores were 1345/2100 (SD = 324) for mini-open patients and 1463(287) for arthroscopic repair. At 1 year, patients in the mini-open group had a mean score of 712.5 (SD = 650.7) and the patients in the all-arthroscopic group had a mean score of 940.6 (a difference of 228 points on the WORC). In our estimates of sample size requirements, we have used an estimated standard deviation of 450 since we suspect that the standard deviation observed in the pilot study at 1 year is larger than that expected at 2 years since patients are expected to be more stable in their outcomes by this time point. Further evidence to support our hypothesis comes directly from our pilot data where the estimate of standard deviations from the baseline assessment was 287 and 325. We will perform an analysis of covariance (ANCOVA) using the baseline WORC scores as a covariate to determine whether there is a statistically significant and clinically important difference between treatment groups at 2 years post-operative. We defined a clinically important difference as a 20% difference in the mean score between groups [47]. We used the following equation to calculate the sample size:

Calculation: N per group = 2((Z_α _+ Z_β_)^2^σ^2^(1-r^2^))/(δ)^2^, Where:

α = the probability of making a Type I error = 0.05

1-β = the power to detect a difference if one truly exists = 0.80, thus, β = 0.20

δ = 20% of the baseline mean score = 142.5*

r = correlation between baseline and post-operative data = 0.55

σ = standard deviation = 450

N per group = 2((1.96 + 0.84)^2 ^(450)^2^(1-0.55^2^))/(142.5)^2 ^= 109 patients per group

Next, we inflated this value by 15% to compensate for patients who will withdraw, who become lost to follow-up, or become procedural crossovers. Thus, the total sample size is 250 patients. If the estimate of standard deviation from our pilot work of 650 is accurate, our study will have 99% power to detect a difference between groups of the magnitude that was observed in our pilot work. This sample size will be also be adequate to detect moderate effects in secondary outcome measures, including self-report, impairment measures, and survey results. It is unlikely that this sample will be sufficient to detect difference in crossover rates as we expect the proportions will be very low. Nevertheless, we feel this is an important outcome to report so that future systematic reviews addressing expertise-based versus traditional randomization can address this issue.

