In our primary analysis we will use an analysis of covariance (ANCOVA), where the baseline WORC score is used as a covariate, to compare the quality of life (WORC score) at 2 years post-operatively[88-91]. As a secondary analysis, we will conduct the same statistical test but will include age and tear size as covariates with the baseline score. All outcome measures with a continuous metric will be analyzed in the same manner (ASES, range of motion, MRI (degree of muscle atrophy, degree of fatty infiltration, remaining tear size), Work Limitations, strength, and SF-12). We will also conduct a repeated-measures ANCOVA to determine whether quality of life (as the primary outcome) changed differently over time between groups.

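### The 99% power claim at SD 650 rests on a raw pilot difference of 228 points, 118 of which were already present at baseline, so it is not the difference the ANCOVA will test

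*Protocol article*

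**What the plan says.** All the figures are in the Protocol article under Sample size.

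- **Pilot design:** "We have previously completed a non-randomized pilot study (n = 36" patients.
- **Baseline:** "the baseline WORC scores were 1345/2100 (SD = 324) for mini-open patients and 1463(287) for arthroscopic repair".
- **One year:** "patients in the mini-open group had a mean score of 712.5 (SD = 650.7"), while "the all-arthroscopic group had a mean score of 940.6 (a difference of 228 points on the WORC"). No 1-year SD is given for the arthroscopic group.
- **Supporting claim:** if the pilot SD of 650 is right, the 250 patients are said to give 99% "power to detect a difference between groups of the magnitude that was observed in our pilot work".

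The same section fixes the analysis: "We will perform an analysis of covariance (ANCOVA) using the baseline WORC scores as a covariate". Planned analyses repeats it: "In our primary analysis we will use an analysis of covariance (ANCOVA), where the baseline WORC score is used as a covariate". The sizing formula carries the matching variance reduction, 1 - r², with r = 0.55.

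The section prints both baseline means. It does not remark that they differ, and it gives no baseline-adjusted pilot difference.

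**The concern.** In a randomized trial the expected baseline difference is zero, and ANCOVA removes whatever chance difference remains. A raw follow-up gap between two non-randomized groups that started apart is a different quantity. Here the arthroscopic group scored higher before surgery and higher at 1 year, so part of the 228 was there before anyone was treated. The plan uses the baseline correlation to shrink the variance, but does not make the correction to the pilot difference that the same correlation implies.

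The sentence matters because the planning SD of 450 is well below the 650.7 seen in the pilot. The plan supports the lower value only by an expectation of more stable outcomes at 2 years and by the smaller baseline SDs. The 99% statement is the only power figure given for the larger SD. A reader could take it to mean that the trial would almost certainly detect what the pilot saw, even with that SD.

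**Working it through.** **Inputs from the Sample size section:** baseline means 1345 and 1463, with SDs 324 and 287; 1-year means 712.5 and 940.6; SD 650; r = 0.55; two-sided α = 0.05 (the formula uses 1.96); 250 patients, so 125 per group at 1:1.

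**Assumptions, not in the document:** SD 650 applies to both groups, and a single correlation r links baseline to follow-up in the pilot. The plan gives r = 0.55 as a planning input and does not attribute it to the pilot, so r is varied below.

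**1. The sample size reproduces.** 2 × (1.96 + 0.84)² × 450² × (1 - 0.55²) / 142.5² = 109.07, stated as 109 per group. 109 × 1.15 × 2 = 250.7, stated as 250. The 228 does not enter.

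**2. The 99% does not reproduce, even for the raw 228.** SE = 650 × √(1 - r²) × √(2/125).
- r = 0.55: SE = 650 × 0.835 × 0.1265 = 68.7; 228.1/68.7 = 3.32; power about 91%.
- r = 0: SE = 82.2; 228.1/82.2 = 2.77; power about 79%.
- With 109 per group and r = 0.55, power is about 87%.
- A value above 99% appears if SD 450 is used with r = 0.55 (99.4% at 109 per group, 99.8% at 125), but that is not the stated condition.

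**3. How much of the 228 was present at baseline.**
- 1-year gap: 940.6 - 712.5 = 228.1.
- Baseline gap: 1463 - 1345 = 118, which is 52% of 228.1.
- Change-score difference: (1345 - 712.5) - (1463 - 940.6) = 632.5 - 522.4 = 110.1.

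**4. Baseline-adjusted difference.** Pooled baseline SD = √((324² + 287²)/2) = 306. The ANCOVA slope is r × 650/306, and the adjusted difference is 228.1 - slope × 118. Power uses 125 per group and the SE from step 2 at the same r.

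| r | slope | adjusted difference | SE | power |
|---|---|---|---|---|
| 0 (no adjustment) | 0 | 228 | 82.2 | 79% |
| 0.3 | 0.64 | 153 | 78.4 | 50% |
| 0.4 | 0.85 | 128 | 75.4 | 40% |
| 0.55 | 1.17 | 90 | 68.7 | 26% |

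The change-score difference of 110, with the SE at r = 0.55, has about 36% power.

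**5. Where the adjusted value crosses the planning difference.** It equals 142.5 when the slope is (228.1 - 142.5)/118 = 0.725, that is r = 0.725 × 306/650 = 0.34. Below that r it is above 142.5; above that r it is below.

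**6. Precision of the pilot.** If the 36 patients were split 18 and 18 (the split is not given), the SE of the adjusted difference at r = 0.55 would be 650 × 0.835 × √(2/18) = 181. A 95% interval around 90 would run from about -265 to 445.

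**The case against.** The strongest reply is that nothing in the design rests on 228. The sample size uses 142.5 and SD 450, and it reproduces. The power sentence is conditional on a difference of the size observed; it does not say that 228 is the expected or adjusted effect. Both baseline means and the non-randomized design are disclosed. Power for a true difference of 228 is a well-defined quantity, and the plain error there is that it is not 99%. All of this stands, and it confines the point to one supporting sentence. It does not rescue the sentence: a pilot difference is worth quoting only as a guide to what the trial's analysis will test, and 228 is not on that scale.

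A reader might go further and infer that the true pilot effect is 90 to 110 points, that the trial has 25% to 35% power for it, and that it lies below the trial's own 142.5. The document does not support this as fact:

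- The 90 depends on r = 0.55, which is not stated to come from the pilot, and on a 1-year SD reported for one group only.
- The 110 is a change-score figure, not an ANCOVA estimate.
- With r below about 0.34 the adjusted difference exceeds 142.5.
- On an even split the interval in step 6 includes 228, and adjusting a non-randomized comparison for baseline need not recover what a randomized trial would estimate.

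Nor does it follow that 250 patients are too few for the trial's stated target.

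**Conclusion.** The point holds in limited form. The 99% figure is tied to an unadjusted 1-year contrast from groups 118 points apart at baseline, while the planned test is baseline-adjusted. The direction is firm: any positive baseline correlation makes the adjusted difference smaller than 228, whether or not a lower WORC score means better. The size is not firm. At SD 650 and 125 per group, power runs from about 50% at r = 0.3 to about 26% at r = 0.55. No correlation from 0 to 0.55 gives the pilot difference, adjusted at that correlation, more than about 79%. These figures assume SD 650 in both groups and 125 analysed per group, which makes no allowance for losses. The sample size, the randomization and the primary analysis are unaffected.

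**What to change.** In the Sample size section, state that 228 is an unadjusted 1-year difference and that the non-randomized pilot groups differed by 118 points at baseline. Then take one of two routes:

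1. Delete the sentence claiming 99% power.
2. Fit the planned ANCOVA to the 36 pilot patients, report the adjusted difference with its confidence interval, and restate the power of 250 patients at SD 650 for that difference, giving the correlation used.

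The values in the working show the likely range. They should not be put into the protocol in place of a fit to the pilot data. No change in sample size is proposed.

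The cost is a wording change and, for the second route, one re-analysis of existing data. The downside is a less favourable stated power.

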**Methods/Design:**

This randomized, multi-centre, national trial will determine whether an arthroscopic or mini-open repair provides better quality of life for patients with small or moderate-sized rotator cuff tears. A national consensus meeting of investigators in the Joint Orthopaedic Initiative for National Trials of the Shoulder (JOINTS Canada) identified this question as the top priority for shoulder surgeons across Canada. The primary outcome measure is a valid quality-of-life scale (Western Ontario Rotator Cuff (WORC)) that addresses 5 domains of health affected by rotator cuff disease. Secondary outcomes will assess rotator cuff functionality (ROM, strength, Constant score), secondary dimensions of health (general health status (SF-12) and work limitations), and repair integrity (MRI). Outcomes are measured at baseline, at 6 weeks, 3, 6, 12, and 24 months post-operatively by blinded research assistants and musculoskeletal radiologists. Patients (n = 250) with small or medium-sized cuff tears identified by clinical examination and MRI who meet eligibility criteria will be recruited. This sample size will provide 80% power to statistically detect  a clinically important difference of 20% in WORC scores between procedures after controlling for baseline WORC score (α = 0.05). A central methods centre will manage randomization, data management, and monitoring under supervision of experienced epidemiologists. Surgeons will participate in either conventional or expertise-based designs according to defined criteria to avoid biases from differential surgeon expertise. Mini-open or all-arthroscopic repair procedures will be performed according to a standardized protocol. Central Adjudication (of cases), Trial Oversight and Safety Committees will monitor trial conduct. We will use an analysis of covariance (ANCOVA), where the baseline WORC score is used as a covariate, to compare the quality of life (WORC score) at 2 years post-operatively. As a secondary analysis, we will conduct the same statistical test but will include age and tear size as covariates with the baseline score. Enrollment will require 2 years and follow-up an additional 2 years. The trial will commence when funding is in place.

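### The design difference of 142.5 WORC points is labelled 20% of the baseline mean, but it is about 10% of the printed baseline means and exactly 20% of the pilot's 1-year mini-open mean

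*Protocol article*

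**What the plan says.** All the figures are in the Sample size section of the protocol article.

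- Pilot baseline: "the baseline WORC scores were 1345/2100 (SD = 324) for mini-open patients and 1463(287) for arthroscopic repair".
- Pilot at 1 year: "patients in the mini-open group had a mean score of 712.5 (SD = 650.7"), against 940.6 in the all-arthroscopic group, a difference the section gives as 228 points.
- A clinically important difference is defined in the text as 20% of the mean score, compared between groups. No reference mean is named.
- In the list of formula inputs, the difference becomes "20% of the baseline mean score = 142.5". An asterisk follows the number, but no note to it appears in the text available.
- The formula then uses 142.5 with an SD of 450 and a correlation of 0.55, giving 109 per group, inflated by 15% to 250 in total.

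The Abstract describes the target as "a clinically important difference of 20% in WORC scores between procedures", again without saying what the 20% is taken of. The Sample size section also says that the 2-year ANCOVA is meant to establish whether the groups differ both significantly and by a clinically important amount.

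**The concern.** The label and the value on the same line cannot both be right on the scale as printed. Someone who takes the label at its word and works out 20% of the baseline means gets a difference nearly twice the one used.

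This matters because the line does two jobs. It says what effect the 80% power refers to, and it is the only number in the article that puts a size on clinical importance for the primary outcome. If its meaning is open, the same 2-year result can be called clinically important or not, depending on whether the reader follows the words or the figure. That choice could then be made after the data are seen.

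**Working it through.** **Inputs, all from the Sample size section:** baseline means 1345 (mini-open) and 1463 (arthroscopic); 1-year means 712.5 (mini-open) and 940.6 (arthroscopic); SD 450; correlation 0.55; z-values 1.96 and 0.84; difference 142.5; inflation 15%.

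**Step 1. Reproduce the plan's figure.** N per group = 2 × (1.96 + 0.84)² × 450² × (1 − 0.55²) / 142.5² = 2 × 7.84 × 202,500 × 0.6975 / 20,306.25 = 109.07. The plan prints 109. Then 109 × 1.15 × 2 = 250.7, which the plan gives as 250. The arithmetic follows correctly from 142.5.

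**Step 2. Which mean gives 142.5?**

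| Reference mean | Value | 20% of it | Ratio to 142.5 |
|---|---|---|---|
| Baseline, mini-open | 1345 | 269.0 | 1.89 |
| Baseline, arthroscopic | 1463 | 292.6 | 2.05 |
| 1 year, mini-open | 712.5 | 142.5 | 1.00 |
| 1 year, arthroscopic | 940.6 | 188.1 | 1.32 |

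Only the 1-year mini-open mean matches, and it matches exactly. In the other direction, 142.5 / 1345 = 10.6% and 142.5 / 1463 = 9.7%, so the number used is about 10% of baseline. On the full scale it is 142.5 / 2100 = 6.8%.

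The pilot's arm sizes are not given, so no properly pooled baseline mean can be formed. The supportable range for 20% of baseline is 269 to 293.

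**Step 3. What the label would imply for size and power.** With the plan's formula and the other inputs unchanged:

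- 269.0 points: 2 × 7.84 × 202,500 × 0.6975 / 269.0² = 30.6, so 31 per group.
- 292.6 points: the same numerator / 292.6² = 25.9, so 26 per group.

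For power, the residual SD is 450 × √0.6975 = 375.8. With 109 analysed per group, the standard error of the difference is 375.8 × √(2/109) = 50.9.

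- 142.5 points: 142.5 / 50.9 − 1.96 = 0.84, power 79.9%.
- 269.0 points: 269.0 / 50.9 − 1.96 = 3.32, power 99.96%.
- 292.6 points: 292.6 / 50.9 − 1.96 = 3.79, power 99.99%.

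With all 250 analysed (125 per group), power is 85.0% for 142.5 and still above 99.9% for 269.0 and 292.6.

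**Step 4. Does the ambiguity reach plausible results?** The pilot's own 1-year difference is 940.6 − 712.5 = 228.1. This lies between the two readings: above 142.5 and below 269.

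**The case against.** The strongest reply is that only one word is wrong. The definition in the text speaks of a 20% difference between groups and does not mention baseline; the Abstract says the same thing more briefly. Both fit 20% of a follow-up mean. On that view 142.5 is the intended threshold and the word baseline is a slip. This may well be so, and it is why the point cannot be put as an error in the number. It does not clear up the line, because the definition names no reference mean, and at 1 year 20% could be 142.5 or 188.1 depending on the arm.

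A second reply is that the asterisk may lead to a note that is not available here. The absence of the note is no fault of the plan, and the note may name the base. On the printed scale, though, no note can make 142.5 equal to 20% of 1345 or 1463.

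A third is that the score may have been reversed, taking 2100 minus the score. The reversed baseline means are 755 and 637, and 20% of these is 151.0 and 127.4, which bracket 142.5. If the 36 pilot patients were split 23 to 13 (an assumption), the weighted baseline is (23 × 1345 + 13 × 1463) / 36 = 1387.6, its reverse is 712.4, and 20% of that is 142.5. This route cannot be excluded. But the section reports unreversed scores throughout and mentions no reversal, and the exact match to a printed mean is the simpler explanation. If reversal was used, the line still needs to say so.

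Finally, Planned analyses contains no margin or confidence-interval rule that uses 142.5. That is correct and limits the consequence: the threshold bears on how the 2-year difference is interpreted, not on the test itself.

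**Conclusion.** The contradiction is certain on the scale as printed: the label gives 269 to 293 points and the formula uses 142.5, a ratio of 1.89 to 2.05.

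A reader might infer more, and the documents do not support it:

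- That the clinical-importance threshold is itself wrong by a factor of two. This holds only if the word baseline governs, and the text does not settle that.
- That the trial is the wrong size. N follows correctly from 142.5, and because the smaller difference was used, the error cannot leave the trial underpowered.

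What remains is a real but contained fault. The only numerical statement of clinical importance for the primary outcome contradicts itself, and a 2-year difference near the pilot's 228 points would be judged differently under the two readings. The power and sample-size figures for 269 to 293 points rest on the plan's own SD of 450 and correlation of 0.55.

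**What to change.** Before results are known, state the design difference as an absolute number of WORC points and name the mean it derives from.

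- **If 142.5 is kept:** relabel it as 20% of the pilot 1-year mini-open mean of 712.5, or 6.8% of the 2100-point scale. Use that number wherever the 20% is cited (Abstract and Sample size) and when judging clinical importance at 2 years. N stays at 109 per group and 250 in total.
- **If 20% of baseline was meant:** state the value (269 to 293, depending on the arm used) and restate the power for 250 patients, which is above 99.9% under the plan's SD and correlation. The text should then also explain why 250 are recruited.
- **If a reversed score was used:** say so, and give the pooled baseline mean and the pilot arm sizes.

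If 142.5 is kept, the cost is wording only. No endpoint, analysis method or allocation changes in any of the three cases.

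### The 99% power quoted for an SD of 650 does not follow from the plan's own formula, which gives about 91% (86% after 15% loss), and the sentence omits the power at that SD for the 142.5 points used to size the trial

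*Protocol article*

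**What the plan says.** All of this is in the Sample size section of the protocol article, except the 1:1 allocation, which is under Arrangements for allocating participants to trial groups.

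- The trial is sized for an ANCOVA on the WORC score at 2 years. The formula is N per group = 2(Zα + Zβ)²σ²(1 − r²)/δ², with Z values of 1.96 and 0.84 and r = 0.55. The result is 109 per group.
- The difference is given as "δ = 20% of the baseline mean score = 142.5".
- The pilot's 1-year SD in the mini-open group was 650.7, but for the calculation "we have used an estimated standard deviation of 450". Two reasons are given: patients should be more stable at 2 years than at 1 year, and the baseline SDs in the pilot were much smaller.
- The pilot means at 1 year were 712.5 (mini-open) and 940.6 (arthroscopic), a difference of 228 points.
- On attrition: "we inflated this value by 15% to compensate for patients who will withdraw, who become lost to follow-up, or become procedural crossovers". The total is 250.
- Then, on the condition that the pilot SD of 650 is right: "our study will have 99% power to detect a difference between groups of the magnitude that was observed in our pilot work".

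**The concern.** The 99% sentence tells the reader what happens if the SD is not 450 but 650. On its face it says that the trial keeps ample power at the larger SD. Two features make that doubtful.

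First, residual variance in the plan's formula grows with the square of the SD. Going from 450 to 650 multiplies it by (650/450)² = 2.09, so a figure as high as 99% with 250 patients needs checking.

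Second, the sentence changes two inputs at once. As the SD rises from 450 to 650, the difference rises from 142.5 to 228. The reader is never shown the larger SD with the difference that the trial was sized to detect.

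The Planned analyses section foresees no interim analysis and stresses an adequately powered 2-year outcome. A reader who accepts the 99% could take the design to be insensitive to the SD, and could later read a null result as stronger evidence than it is.

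**Working it through.** **Inputs.** Two-sided α = 0.05 (Z = 1.96); r = 0.55; 250 patients at 1:1, so 125 per arm; allowance of 15%; sizing difference 142.5; pilot difference 940.6 − 712.5 = 228.1, stated as 228; SD 450 (design) and 650 (pilot).

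**Step 1: reproduce the plan's sample size.** 2 × (1.96 + 0.84)² × 450² × (1 − 0.55²) / 142.5² = 109.07, stated as 109. Then 109 × 1.15 × 2 = 250.7, stated as 250. So the formula is being read as the authors used it.

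**Step 2: solve the same formula for power.** Power = Φ(δ/SE − 1.96), with SE = σ × √(1 − r²) × √(2/n) and √(1 − 0.3025) = 0.835.

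At SD 650 with 125 per arm:
- SE = 650 × 0.835 × √(2/125) = 68.7
- δ = 228: 228/68.7 = 3.32, and Φ(3.32 − 1.96) = 91.3%
- δ = 142.5: 142.5/68.7 = 2.08, and Φ(0.115) = 54.6%

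At SD 650 after 15% loss, 125 × 0.85 = 106.25 per arm:
- SE = 74.5
- δ = 228: Φ(3.06 − 1.96) = 86.5% (86.46% before rounding, hence about 86%)
- δ = 142.5: Φ(1.91 − 1.96) = 48.1%

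**Step 3: smallest difference detectable with 80% power at SD 650.** 2.80 × 68.7 = 192 points with 125 per arm; 2.80 × 74.5 = 209 points after loss.

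**Step 4: does another reading of the inputs give 99%?** All rows use δ = 228.

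| Variant | Power |
|---|---|
| SD 650, 125 per arm, by noncentral t | 91.1% |
| SD 650, 109 per arm | 87.3% |
| SD 650, 125 per arm, one-sided | 95.3% |
| SD 650, 125 per arm, no baseline adjustment | 79.2% |
| SD 650, 125 per arm, 1 − r in place of 1 − r² | 98.5% |
| SD 650, 125 per arm, factor 2 omitted | 99.7% |
| SD 650, 250 per arm | 99.7% |
| SD 450, 109 to 125 per arm | 99.4% to 99.8% |

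The rows that come near 99% each depart from the printed formula, the stated total or the sentence's own premise of SD 650. A correlation of about 0.76 would also give 99%, but the plan states 0.55. With the printed inputs, 99% would need about 209 patients per arm.

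**The case against.** **The sentence is a side remark.** It follows a sample size that is already fixed and that reproduces. No test or decision rule depends on it, and the corrected 91% or 86% is still above 80% for the scenario it names. All of this stands. It limits the consequence but does not make 99% right.

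**The 142.5-point scenario is not what the sentence describes, and 142.5 is itself unsettled.** The plan calls it 20% of the baseline mean, but 20% of the pilot baseline means (1345 and 1463) is 269 to 293. The figure 142.5 equals 20% of 712.5, the 1-year mini-open mean. For 269 to 293 points, power at SD 650 with 125 per arm would be 97.5% to 98.9%. So the 55% and 48% must be stated as conditional on 142.5. That condition is reasonable, because 142.5 is the number that was put into the calculation. Nor do the higher figures rescue the sentence, which refers to the difference observed in the pilot, 228.

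**The SD of 650 may not apply.** It comes from one arm of a 36-patient pilot at 1 year, while the endpoint is at 2 years, and the plan gives its reasons for using 450. This stands too. A reader might infer from the 55% that the trial is underpowered, or that the 99% sentence is all that supports the choice of 450. The document supports neither inference. The point concerns what follows if the SD is 650, which is the condition that the sentence itself sets.

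**The pilot difference might shrink under ANCOVA.** The pilot's arthroscopic group started 118 points higher (1463 v 1345), so a reader might infer that the planned ANCOVA would see much less than 228. The size of that change cannot be derived from the document. It needs an assumed slope: with slope r × 650.7/305.5 (305.5 being the average of the baseline SDs 324 and 287), the adjusted gap runs from about 90 points at r = 0.55 to about 153 at r = 0.3. The sentence speaks of the observed magnitude, so 228 is the right figure for checking it.

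**Conclusion.** The 99% is wrong as written. With the plan's own formula and inputs, power for 228 points at SD 650 is about 91% if all 250 are analysed and about 86% after 15% loss. The chance of missing such a difference is therefore about 9% to 14%, not 1%. At the same SD, power for the 142.5 points used to size the trial is about 55%, or 48% after loss.

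These figures assume a common SD of 650 in both arms, as the sentence does (a 1-year SD is printed for mini-open only), and r = 0.55 at that SD. The lower figures treat the whole 15% as lost from analysis. Since the allowance also covers crossovers, who may still supply outcome data, they are the pessimistic end.

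How the 99% arose cannot be determined. Several different slips would produce a figure near it, and the document does not favour any one of them.

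**What to change.** Delete the 99% claim in the Sample size section and put in its place:

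> If the SD is 650, power is about 91% (86% after 15% loss) for 228 points and about 55% (48% after 15% loss) for the 142.5 points used in the sample size calculation; the smallest difference detectable with 80% power is about 190 to 210 points.

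Optional minor note: multiplying 109 by 1.15 gives 125 per arm, which leaves 106 after a full 15% loss, whereas 109/0.85 would give 129. Base-case power at SD 450 and 142.5 points is then 79% rather than 80%. The gap is too small to need action.

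The cost is wording only. No patients are added, and neither the design nor the analysis changes. The one consequence is that a stated figure becomes less favourable.
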